# Shaping anesthetic techniques to reduce post-operative delirium (SHARP) study: a protocol for a prospective pragmatic randomized controlled trial to evaluate spinal anesthesia with targeted sedation compared with general anesthesia in older adults undergoing lumbar spine fusion surgery

**DOI:** 10.1186/s12871-019-0867-7

**Published:** 2019-10-27

**Keywords:** Spinal, General, Anesthesia, Lumbar, Spine, Surgery, Delirium, Post-operative

## Abstract

**Background:**

Postoperative delirium is common in older adults, especially in those patients undergoing spine surgery, in whom it is estimated to occur in > 30% of patients. Although previously thought to be transient, it is now recognized that delirium is associated with both short- and long-term complications. Optimizing the depth of anesthesia may represent a modifiable strategy for delirium prevention. However, previous studies have generally not focused on reducing the depth of anesthesia beyond levels consistent with general anesthesia. Additionally, the results of prior studies have been conflicting. The primary aim of this study is to determine whether reduced depth of anesthesia using spinal anesthesia reduces the incidence of delirium after lumbar fusion surgery compared with general anesthesia.

**Methods:**

This single-center randomized controlled trial is enrolling 218 older adults undergoing lumbar fusion surgery. Patients are randomized to reduced depth of anesthesia in the context of spinal anesthesia with targeted sedation using processed electroencephalogram monitoring versus general anesthesia without processed electroencephalogram monitoring. All patients are evaluated for delirium using the Confusion Assessment Method for 3 days after surgery or until discharge and undergo assessments of cognition, function, health-related quality of life, and pain at 3- and 12-months after surgery. The primary outcome is any occurrence of delirium. The main secondary outcome is change in the Mini-Mental Status Examination (or telephone equivalent) at 3-months after surgery.

**Discussion:**

Delirium is an important complication after surgery in older adults. The results of this study will examine whether reduced depth of anesthesia using spinal anesthesia with targeted depth of sedation represents a modifiable intervention to reduce the incidence of delirium and other long-term outcomes. The results of this study will be presented at national meetings and published in peer-reviewed journals with the goal of improving perioperative outcomes for older adults.

**Trial registration:**

Clinicaltrials.gov, NCT03133845. This study was submitted to Clinicaltrials.gov on October 23, 2015; however, it was not formally registered until April 28, 2017 due to formatting requirements from the registry, so the formal registration is retrospective.

## Background

Post-operative delirium is a common occurrence in the elderly, with frequency estimates ranging from 10 to 50%, depending on the type of surgery [1]. For older adults undergoing spine surgery in particular, the incidence of delirium has been estimated to be > 30% [2]. This is a concern given that spine surgery is one of the top five procedures performed in this population [3]. Although previously thought to be transient with few long-term effects, it is now evident that delirium is associated with significant morbidity, including decreased functional status [4], increased duration of hospitalization [2, 5], increased mortality [6, 7], and cognitive decline [8–10]. In spite of the importance of postoperative delirium, there are few effective strategies to prevent delirium and long-term complications in older adults undergoing surgery.

Optimizing depth of anesthesia may represent a modifiable strategy for the prevention of delirium, with the hypothesis that excessive depth of anesthesia may have deleterious consequences for older adults. There are several potential mechanisms to support this hypothesis. In laboratory models, anesthetic agents have been shown to be neurotoxic, due to multiple mechanisms including enhanced neuronal apoptosis [11, 12], increased oligomerization and production of Alzheimer’s-associated amyloid-β protein [11, 12], and increased phosphorylation of Tau [13]. In clinical investigations, substantial anesthetic exposure may result in burst suppression on the electroencephalogram (EEG), and observational studies have shown an association between duration of burst suppression and mortality and delirium [14, 15], although a randomized trial showed no reduction in delirium from avoidance of burst suppression [16]. Finally, due to the hypotensive effects of anesthetic agents, EEG patterns consistent with deep anesthesia may in fact reflect inadequate cerebral blood flow [17].

In current practice, depth of anesthesia is determined by direct observation of hemodynamic and other autonomic responses to surgery, or with monitoring of the processed EEG (e.g., Bispectral Index [BIS], Medtronic, Inc., Andover, MA). The BIS monitor is a processed electroencephalogram which incorporates time-domain, frequency-domain, and bispectral analysis of raw EEG signals, and displays a dimensionless number ranging from 0 (isoelectric) to 100 (fully awake), with values < 60 consistent with general anesthesia [18, 19].

Prior to 2017, four randomized trials had demonstrated that using BIS to minimize the depth of anesthesia could reduce postoperative delirium [20–23]. Based on these trials, guidelines recommended that depth of anesthesia monitoring could be considered [24]. However, two recent trials using BIS or EEG-guidance during anesthesia failed to show a reductions in the frequency of delirium compared with standard care [16, 25]. Thus, the results of this body of literature are conflicting as to whether minimizing depth of anesthesia by monitoring processed EEG reduces the risk for postoperative delirium. Nonetheless, there are several points to consider in interpreting these data. First, in the majority of trials [16, 21–23], all patients received general anesthesia, and despite processed EEG monitoring, the intervention groups were maintained at a deep plane of anesthesia. Two other studies were conducted in patients undergoing spinal anesthesia for hip fracture surgery and randomization to “deep” vs. “light” sedation [20, 25]. However, the results were conflicting with one trial reporting a reduction in delirium in the “light” sedation group, but a follow-up study showing no difference. Of note, patients undergoing hip fracture have a high prevalence of dementia and 1-year mortality greater than 20% [26], and so results in this population would not be generalizable to most older adults undergoing surgery.

Thus, there is a clear need for further studies to determine whether reducing depth of anesthesia (beyond levels consistent with general anesthesia) can reduce delirium in a patient population that is generalizable to older adults whom are most susceptible to this complication. From a long-term perspective, it is unclear if preventing delirium may be a strategy to prevent cognitive and functional decline after hospitalization, and thus further study is needed to examine this question.

To address these gaps in understanding we are conducting the SHARP study, a prospectively randomized trial to determine whether reducing depth of anesthesia in the context of spinal anesthesia with targeted sedation versus general anesthesia can reduce the incidence of delirium after spine surgery in older adults. Spine surgery was chosen because of the high volume of the procedure in older adults and the associated high incidence of delirium. The study design is pragmatic since the interventions for each experimental group are bundled: the intervention arm receives spinal anesthesia with reduced depth of anesthesia [BIS targeted> 60–70] and propofol sedation, while the control arm receives general (deep) anesthesia with a volatile anesthetic. Because of the bundled interventions, depth of anesthesia will be linked with anesthetic technique. With regards to anesthetic technique, a large number of prior studies and meta-analyses have suggested that regional or neuraxial anesthesia does not reduce the incidence of delirium in comparison with general anesthesia [27, 28]. Similarly, there is no convincing evidence that intravenous anesthesia in comparison with volatile anesthesia reduces the incidence of delirium, although the quality of evidence is noted to be low [29, 30]. However, the depth of anesthesia was not accounted for in many of these studies, and is a key intervention in the current study, thus motivating the design and conduct of this trial. In the SHARP study, we will obtain preliminary data on whether a bundled intervention to reduce depth of anesthesia can improve cognition, functional status, disability, health-related quality of life, health care utilization, and pain at 3- and 12-months after surgery. In particular, there is some evidence that preemptive analgesia can reduce immediate postoperative analgesia requirements but long-term effects of pre-emptive analgesia are unclear, thus highlighting the importance of collecting pain and functional outcomes after discharge [31]. The primary hypothesis of the SHARP study is that reducing depth of anesthesia by using spinal anesthesia with targeted sedation will reduce the incidence of delirium after spine surgery in older adults compared with general anesthesia. The main secondary hypothesis is that the reduced depth of anesthesia group will have improvements in a screening measure of cognition compared to baseline.

## Methods/design

### Trial design and overview

The SHaping Anesthetic techniques to Reduce Postoperative delirium (SHARP) study is a single-center, prospective, randomized controlled superiority trial with two parallel groups. An overview of study procedures is shown in Fig. 1. The trial is enrolling patients 65 years and older undergoing lumbar spine fusion surgery. Participants are randomly assigned in a 1:1 allocation to spinal anesthesia with targeted intravenous sedation (intervention) or general anesthesia (control group). Assessments are conducted at baseline, in-hospital after surgery, and at 3- and 12- months after surgery. The primary outcome is the incidence of postoperative delirium. Secondary outcomes include the domains of cognition, function, disability, health-related quality of life, health care utilization, and pain.

**Fig. 1 Fig1:**
[figure not shown]
Study Flow Diagram. A flow diagram of study procedures is shown, including screening, enrollment, randomization, intervention, and follow-up assessments

### Study setting

The trial is being conducted at Mercy Medical Center in Baltimore, MD. The target completion date for study activities is June 2020.

### Eligibility criteria

Inclusion criteria for participation in the study are: 1) age 65 years or older, 2) undergoing a lumbar spine fusion surgery, 3) expected duration of surgery < 3 h, 4) under the care of a participating surgeon, and 5) expected ability to understand and comply with study procedures. Exclusion criteria are: 1) contraindications to spinal anesthesia (e.g. severe aortic stenosis, anti-coagulant or anti-platelet therapy), 2) BMI > 40, 3) prior L2–5 full lumbar fusion, 4) communication issues precluding baseline assessments, 5) baseline dementia or MMSE < 24, 6) psychiatric disease that would preclude cooperation with sedation with spinal anesthesia, and 7) attending surgeon or anesthesiologist preference for either spinal or general anesthesia for any reason due to clinical considerations.

### Patient recruitment

Research assistants screen patients for eligibility before scheduled surgery. Eligible patients are approached prior to surgery to discuss the study, and written informed consent is obtained prior to any study procedures by research staff. There are no financial incentives provided to patients. Before randomization, all clinicians (surgeons and anesthesiologists) are given the opportunity to withdraw the patient from the study for any reason, in particular if it is felt that the patient would clinically benefit from either general anesthesia or spinal anesthesia.

### Assignment of intervention

A computer-generated randomization list was created by a research nurse prior to initiation of the study. For the purpose of allocation concealment, patient assignments are placed in sealed opaque envelopes, which are sequentially opened by clinical staff after randomization, prior to entering the operating room.

### Intervention and control

The intervention group receives spinal anesthesia with targeted sedation, while the control group receives general anesthesia. To measure depth of anesthesia, all patients are monitored with a Bispectral Index (BIS) monitor. The BIS monitor is FDA-approved to monitor depth of anesthesia and displays a unit-less number (0–100) derived from processed EEG waveforms. BIS values between 40 and 60 are consistent with general anesthesia.

In the intervention group, spinal anesthesia is obtained through injection of 10–15 mg of bupivacaine into the subarachnoid space. Lidocaine may also be used for at the discretion of the attending anesthesiologist, based on the expected length of the surgical procedure. During the surgery, patients receive sedation with propofol (generally 25–150 mcg/kg/min), with guidance for sedation to be targeted to a BIS > 60–70. However, the anesthesiologist is instructed to prioritize any clinical concerns in the case that depth of sedation needs to be increased based on clinical judgment. In the event that the duration of the surgical procedure exceeds the analgesic effect of the spinal anesthetic, the surgeon will inject further intrathecal anesthetic under direct visualization, in consultation with the anesthesiologist.

In the control group, patients receive general anesthesia with an endotracheal tube. Guidelines are for anesthetic induction with propofol (generally 1–2 mg/kg) or etomidate, maintenance with a volatile anesthetic, muscle relaxation with a non-depolarizing muscle relaxant, and analgesia generally with fentanyl (generally 2–5 mcg/kg titrated). Hydromorphone and/or morphine is also acceptable. Patients on baseline opioids may receive additional opioids based on clinical criteria. Although patients under general anesthesia are also monitored with BIS, the anesthetic provider is masked to BIS values unless there is clinical need based on the individual anesthesiologist.

### Masking

Delirium outcome assessors are masked to the intervention. Postoperative data is abstracted from the electronic medical record by staff masked to the intervention. The assessments at 3- and 12- months are not masked. Throughout the study, patients, surgeons, and anesthesiologists are not masked, because it is virtually impossible for the anesthetic technique to be masked to treating physicians or patients. Statisticians and investigators involved in data analysis will be masked.

### Perioperative management

Perioperative care is according to clinical protocols at the Mercy Medical Center. Depending on the usual practice of the attending spine surgeon, patients may receive intrathecal opioids (generally 0.2–0.4 mg morphine) or local anesthetic. Patients receive fentanyl in the recovery room for pain. On the floor, patients use fentanyl or hydromorphone patient-controlled analgesia and transition to oxycodone or other oral opioids as tolerated.

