### Other secondary outcomes

Additional domains that are important for postoperative recovery will be examined as secondary outcomes. These domains include: duration and severity of delirium, other tests of cognition, functional status, disability, health-related quality of life, health care utilization, and pain. The specific tests and outcomes for each of these domains are listed and defined in Table 2.

**Table 2 Tab2:** Primary and Secondary Outcomes

Domain	Outcome	Definition
Delirium	Incident delirium *(Primary Outcome)*	Any CAM (+) assessment
	Delirium severity	Maximum DRS-R-98 score
	Number of days of delirium	Number of CAM (+) days
Cognition	Change in MMSE/TICS	Change in score. Item response theory will be used to compare similar or exact items if TICS> 50% of responses.
	Change in other individual test scores	Verbal Fluency (all trials combined, sum of scores), TMT-A (time), TMB-B - TMT-A (time), DSF (longest span correct), DSB (longest span correct)
Function	Any decline in IADL score	Any decline in IADL score from baseline to 3- and 12-month follow-up
Disability	Change in ODI score	Change in ODI score (%) from baseline to 3- and 12-month follow-up
Health-Related Quality of Life	Change in SF-12 PCS	Change in PCS score from baseline to 3- and 12-month follow-up
	Change in SF-12 MCS	Change in MCS score from baseline to 3- and 12-month follow-up
Health Care Utilization	Readmissions	% Readmissions
	Emergency department visits	% Emergency department visits
	Duration of hospitalization	Number of days in hospital after surgery
Pain	PACU pain	Last pain score in PACU.
		Total morphine equivalents
		Time to first opoid
	Hospital pain	Last pre-discharge pain score.
		Total morphine equivalents, pro-rated for 72 h in hospital
	Post-discharge pain	Average pain score at 3- and 12-month follow-up

Abbreviations: *CAM* Confusion Assessment Method, *DRS-R-98* Delirium Rating Scale-Revised 1998, *MMSE* Mini-Mental State Examination, *TMT* Trail Making Test, *DSF* Digit Span Forward, *DSB* Digit Span Backwards, *IADL* Instrumental Activities of Daily Living, *ODI* Oswestry Disability Index, *SF-12* 12-Item Short Form Health Survey, *PCS* physical component summary, *MCS* mental component summary, *PACU* postoperative anesthesia care unit

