It is expected that < 10% of patients randomized to receive spinal anesthesia will actually receive general anesthesia due to failure to obtain spinal anesthesia. If patients receive both a spinal and general anesthetic, they will be categorized into an appropriate group for the on-treatment approach based on the biologic hypothesis for each analysis. For the purposes of the primary analysis on-treatment approach, they will be considered to have received deep anesthesia.

In a sensitivity analysis, we will consider accounting for crossover based on an inverse-probability of treatment weighting approach. This approach will provide an estimate of the difference in the incidence of delirium comparing the intervention and control groups, had all patients received their randomized treatment. Other sensitivity analyses will include: a) an as-treated analysis, b) re-estimation of both of the above treatment effects after adjustment for select baseline covariates, including age, education, and cognitive score [36], with consideration of gender, race, and other variables associated with incidence of delirium in bivariate analyses, and c) pre-specified subgroup analyses based on stratifying patients by age (< 75 vs. > 75 years old), baseline Charlson Comorbidity Index (0 vs. > 0), and baseline cognition (MMSE < 27 vs ≥27, or lowest quartile vs upper quartiles, dependent upon the baseline distribution). Confidence intervals and *p*-values will be generated via a bootstrap procedure using 5000 bootstrap samples.

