The most important secondary outcome is change in MMSE (or Telephone Interview for Cognitive Status [TICS]) [37]. Change in MMSE/TICS will be analyzed using linear regression analysis, first unadjusted, and then with adjustment for age and education, with consideration of gender, race, and other variables associated with change in MMSE/TICS in bivariate analyses. If TICS is > 50% of responses, we will use item response theory to compare similar or exact items on the TICS and MMSE. The treatment effect will be defined as the difference in the change in MMSE/TICS at three months comparing the intervention and control groups. Other pre-specified secondary outcomes that will be compared between groups by domain are listed in Table 2 and include: (1) delirium severity and number of days of delirium, (2) change in each individual cognitive test score), (3) change in function, disability and quality of life (Instrumental Activities of Daily Living score [38] [any decline], Oswestry Disability Index score [39], Short Form (SF)-12 Physical Component Summary, SF-12 Mental Component Summary [40], (4) hospital utilization (readmissions, emergency department visits, duration of hospitalization, and (5) pain (pain in the postoperative anesthesia care unit, hospital pain, and post-discharge pain. The main post-discharge outcomes will be measured at 3-months. However, we will also collect and report data at 12-months after surgery. For continuous and binary secondary outcomes, similar methods as described above will be applied. We anticipate that delirium severity and number of days of delirium will be highly skewed and will be analyzed as ordinal or dichotomous variables.

Other pre-specified analyses include examining (1) the association of delirium and hospital utilization and other post-discharge outcomes (2) the association of BIS values and burst suppression with postoperative delirium and cognitive change, and (3) risk factors for decline in cognition, function, or health-related quality of life after spine surgery. In all analyses, a value of *p* < 0.05 will be considered significant. Due to the number of outcomes that will be examined (beyond incident delirium and change in MMSE), the analyses of secondary outcomes will be considered preliminary and hypothesis-generating.

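### Attending surgeon, whose habit decides intrathecal drug use, should be a fixed covariate in the adjusted in-hospital pain and opioid models, not left to a bivariate screen

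*Protocol article*

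**What the plan says.** - **Source of variation.** Under Perioperative management: "Depending on the usual practice of the attending spine surgeon, patients may receive intrathecal opioids (generally 0.2–0.4 mg morphine) or local anesthetic". The sentence names neither arm and gives no frequency.
- **Surgeon is a baseline variable.** One inclusion criterion is being "under the care of a participating surgeon", so the surgeon is known before allocation.
- **Outcomes exposed to it.** The pain rows of Table 2 list the last recovery-room pain score, recovery-room morphine equivalents, time to first opioid, the last pain score before discharge, and "Total morphine equivalents, pro-rated for 72 h in hospital".
- **Covariates.** For delirium, Data and statistical analysis plans "adjustment for select baseline covariates, including age, education, and cognitive score [36], with consideration of gender, race, and other variables associated with incidence of delirium" on bivariate testing. For MMSE change the named covariates are age and education, with the same kind of screen for others. For the remaining outcomes: "For continuous and binary secondary outcomes, similar methods as described above will be applied". Surgeon is not named in any of these places.
- **Status.** The same section treats secondary outcomes beyond MMSE change as hypothesis-generating.

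**The concern.** The article identifies one factor that determines whether a patient gets a drug acting directly on early pain and opioid need: the habit of the attending surgeon. It then carries over to those outcomes an adjustment set built for delirium and cognition. Age, education and baseline cognition are sensible there, but they do not capture differences between surgeons in analgesic practice.

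Surgeon can still enter as one of the other variables, but only if its observed association with the outcome passes the bivariate screen. That has two drawbacks. A real but moderate surgeon effect spread over several surgeons may fail the screen, and its variance then stays in the residual. The final model also depends on the outcome data, although this variable was known to be relevant in advance.

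At stake is the width of the confidence intervals for pain and opioid use. The article's background invokes pre-emptive analgesia as a reason to collect pain outcomes, so these comparisons should be made as precise as the data allow.

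**Working it through.** **Inputs from the article (Sample size):** delirium 35% in controls and a 50% reduction, so 17.5% in the intervention arm; significance level 0.05 (taken as two-sided); power 0.80; 206 evaluable patients, 103 per arm at 1:1.

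**Not in the documents:** number of surgeons, frequency of intrathecal use, and standard deviations of the pain and opioid outcomes. The share *r* of within-arm outcome variance due to surgeon is therefore an assumption, shown over 2–20%.

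**Step 1: reproduce the stated 206.** With the log-odds-ratio formula:

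n per arm = (1.960 + 0.842)² × [1/(0.35 × 0.65) + 1/(0.175 × 0.825)] / [ln(odds ratio)]²

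= 7.849 × (4.396 + 6.926) / 0.9316² = 102.4, so 103 per arm and 206 in total. The stated figure reproduces, and nothing below changes it.

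**Step 2: detectable difference on a continuous outcome without surgeon.**

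(1.960 + 0.842) × √(2/103) = 0.390 standard deviations at 80% power.

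**Step 3: the same with surgeon as a covariate.** The residual standard deviation falls by the factor √(1 − r), so:

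- reduction in standard error = 1 − √(1 − r)
- equivalent unadjusted sample size = 206/(1 − r)
- power for a 0.390 difference = Φ(2.802/√(1 − r) − 1.960)

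| Assumed r | SE reduction | Equivalent N | Detectable difference | Power |
|---|---|---|---|---|
| 0 | 0% | 206 | 0.390 | 80.0% |
| 0.02 | 1.0% | 210 | 0.386 | 80.8% |
| 0.05 | 2.5% | 217 | 0.381 | 82.0% |
| 0.10 | 5.1% | 229 | 0.370 | 84.0% |
| 0.20 | 10.6% | 258 | 0.349 | 87.9% |

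**Step 4: an illustration of r.** Suppose half the patients have a surgeon who uses intrathecal drug, and its effect is 0.5 within-group standard deviations (both assumed). The added variance is 0.5 × 0.5 × 0.5² = 0.0625, so r = 0.0625/1.0625 = 5.9%. Leaving surgeon out then inflates the standard error by √1.0625 − 1 = 3.1%.

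**Step 5: the cost.** As an approximation, each surgeon term costs about one patient's worth of information. At r = 0.02 the gain is worth 210 − 206 = 4 patients, so about four terms would use it up. At r = 0.10 it is worth 229 − 206 = 23 patients, and a few terms cost little by comparison.

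These formulas are for continuous outcomes. For time to first opioid they indicate the direction and rough size only.

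**The case against.** **This belongs to an analysis plan that is not shown.** The covariate list is open, and a condensed article may leave details for secondary outcomes to a fuller document. That limits the weight of the point. What remains is that the article does fix a route for this variable, an outcome-dependent screen, and carries it over to outcomes for which it has itself described surgeon practice as a source of variation.

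**The size is assumed.** This stands: the documents contain nothing from which to estimate the variance share, and at the low end the gain is negligible.

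A reader might also infer four stronger things, which the documents do not support.

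- *Uncounted contamination of the control arm.* Intraoperative medications are abstracted (Data collection). The rule for patients who get a spinal as well as a general anesthetic is not limited to one arm and lets classification follow the hypothesis of each analysis, so no new as-treated reclassification is needed. It is true that "It is expected that < 10% of patients randomized to receive spinal anesthesia will actually receive general anesthesia due to failure to obtain spinal anesthesia" speaks of one direction only, but the rule that follows it does not. The route of the local anesthetic is ambiguous in the sentence quoted above. Intrathecal drug under general anesthesia also does not deliver the reduced anesthetic depth that defines the intervention.
- *Randomization was not stratified by surgeon.* The article says "A computer-generated randomization list was created by a research nurse prior to initiation of the study" and neither states nor denies strata. Silence is not evidence of absence.
- *Bias.* A surgeon's habit applied alike in both arms is balanced in expectation by randomization, and chance imbalance is already reflected in the unadjusted standard error. Surgeons are unmasked, so use could differ by arm, but no passage says that it does, and surgeon adjustment would not remove such a difference.
- *The delirium model needs surgeon too.* Under the article's own assumptions there are about 103 × 0.35 + 103 × 0.175 = 54 events, to be shared with an unknown number of surgeon terms. That extension is debatable and is not claimed here.

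**Conclusion.** The point holds as a minor gain in precision. Surgeon is known at baseline, is plausibly prognostic for early pain and opioid use on the article's own description, and is left to a bivariate screen. With an assumed surgeon variance share of 2–20%, fixing it as a covariate gives about a 1–11% smaller standard error, or 1–8 points of power for a 0.390 standard-deviation difference at 103 per arm, before the small cost of the extra terms. The true share is unknown. Only the adjusted in-hospital pain and opioid analyses are affected, and the article already treats these as hypothesis-generating. The unadjusted comparisons stay valid, and the primary delirium analysis and the N of 206 do not change.

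**What to change.** 1. In the adjusted models for recovery-room and hospital pain scores, morphine equivalents and time to first opioid, pre-specify attending surgeon as a fixed covariate, in place of reliance on the bivariate screen. State in advance the volume below which surgeons are pooled into one category.
2. Report intrathecal opioid and local anesthetic use by randomized arm. Do not adjust for either: they are given after randomization, so adjustment could remove part of the treatment effect or introduce bias.

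**Cost:** analysis-plan wording and a few degrees of freedom. Intraoperative drugs are already abstracted. Surgeon is not listed by name among the abstracted items, but should be identifiable because eligibility depends on it. No change to clinical care, to the primary analysis or to the sample size is involved.
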